**Table 1 Tab1:**
[figure not shown]
Example of playground games ranked by oxygen consumption and energy expenditure with accelerometer counts and heart rate data also displayed for the HEPAFIT study

*EE* energy expenditure, *HIPE* high-intensity physical education, *LIPE* low-to-moderate intensity physical education

The data for each game is an average for 5 ± 1 subjects (with standard error).  Games with VO_2_ up to 20 mL kg^–1^ min^–1^.  Games with VO_2_ between 20 and 30 mL kg^–1^ min^–1^.  Games with VO_2_ above 30 mL kg^–1^ min^–1^. A full description for the preparation and administration of these games can be found at www.movidavida.org. Table taken from Cañete-García et al. [34]

### Training intensity and energy expenditure during training

Training intensity will be assessed using the mean HR measured in the HIPE, LIPE or combined groups. The exercise training program will be 100% supervised. Attendance at supervised sessions includes compliance with target HR and energy expenditure and will be monitored and recorded by research staff. Energy expenditure will be estimated during exercise via indirect calorimetry using a Cosmed K-5*b*^2^ portable metabolic system (Rome, Italy), assuming a non-protein respiratory exchange ratio [35]. This procedure will be assessed for 30% of participants to help to maintain compliance and to provide a detailed description of each playground games session. It is expected that the gradual increase in total energy expenditure will minimize fatigue, soreness, injuries, and attrition.

### Data collection and outcome measures

Outcome measures will be assessed at baseline and at the end of the 6-month intervention by personnel blinded to the treatment allocation. Data will be recorded on standardized forms and entered into a secured Access database that contains quality control checks (e.g., range checks and notifications for missing data) (Fig. 2). Post-intervention measurements will be scheduled within 7 days following the last exercise session or last supervised program session in the exercise and control groups, respectively.

**Fig. 2 Fig2:**
[figure not shown]
Schedule of enrolment, intervention, and assessment in the HEPAFIT study, according to the SPIRIT 2013 statement

The primary outcome measure is hepatic fat content, which will be assessed with the controlled attenuation parameter. The secondary outcomes of this study will test the additional effects of exercise training on traditional cardiometabolic risk factors [body composition, blood pressure, glycohemoglobin (HbA1c), serum lipids, and insulin resistance] and non-traditional cardiometabolic risk factors (visceral adiposity, endothelial function, cytokines, adipokines, aminotransferases, inflammatory biomarkers, uric acid, ferritin, albumin, and cardiorespiratory and muscular fitness). Also, we include neuronal function biomarkers as measured by neurotrophin-3 (NT-3), neurotrophin-4 (NT-4), and brain-derived neurotrophic factor (BDNF) levels (second secondary objective). Finally, attention capacity and psychological measurements will be assessed to evaluate the additional effect of the exercise intervention on the executive function, quality of life, self-esteem, and well-being of overweight and obese participants. Other covariables of interest include pubertal development, physical activity levels, sedentary behavior, dietary assessment, demographic characteristics, and side effects (Table 2).

**Table 2 Tab2:** Overview of the measurements and methodology at baseline and post-test in the HEPAFIT study

Measure	Methodology
Primary outcome	
Hepatic fat (%)	Vibration-controlled transient elastograph
Secondary outcomes	
Body mass (kg)	Scale
Height (cm)	Stadiometer
Waist circumference (cm)	Non-elastic tape
Blood pressure	Oscillometric monitor device
Heart rate	Oscillometric monitor device
Lean mass (kg), total body fat (%), bone mineral density (g/cm^2^), abdominal adiposity (g), truncal adiposity (g), limb adiposity (g)	Dual X-ray absorptiometry
Visceral adiposity (cm^2^)	Bioelectrical impedance
High-density lipoprotein cholesterol (mg/dL), low-density lipoprotein cholesterol (mg/dL), total cholesterol (mg/dL), total triglycerides (mg/dL), serum glucose (mg/dL)	Enzymatic spectrophotometry
Serum insulin (mU/L)	Electrochemiluminescence immunoassay
Glycohemoglobin (mg/dL)	Electrochemiluminescence immunoassay
Alanine (U/L), aspartate (U/L), gamma-glutamyl transferase (U/L)	Enzymatic assay
Uric acid, albumin (mg/dL), ferritin (mg/dL)	Enzymatic assay
hs-C reactive protein, ENA-78, GCSF, GM-CSF, GRO, GRO-α, I-309, IL-1α, IL-1β, IL-2, IL-3, IL-4, IL-5, IL-6, IL-7, IL-8, IL-10, IL-12 p40/p70, IL-13, IL-15, IFN-γ, MCP-1, MCP-2, MCP-3, MCSF, MDC, MIG, MIP-1β, MIP-1δ, RANTES, SCF, SDF-1, TARC, TGF-β1, TNF-α, TNF-β, EGF, IGF-I, angiogenin, oncostatin M, thrombopoietin, VEGF-A, PDGF-BB, leptin, BLC, Ckß8–1, eotaxin, eotaxin-2, eotaxin-3, FGF-4, FGF-6, FGF-7, FGF-9, Flt-3 ligand, fractalkine, GCP-2, GDNF, HGF, IGFBP-1, IGFBP-2, IGFBP-3, IGFBP-4, IL-16, IP-10, LIF, LIGHT, MCP-4, MIF, MIP-3α, NAP-2, osteopontin, osteoprotegerin, PARC, PLGF, TGF-β2, TGF-β3, TIMP-1, TIMP-2 (mean spot pixel densities)	Proteome Profiler human cytokine array panel A kit
NT-3, NT-4, BDNF (pg/mL)	Surface plasmon resonance biosensors
Flow-mediated dilation	High-resolution ultrasound device
Carotid intima-media thickness	High-resolution ultrasound device
Cardiorespiratory fitness	20-m shuttle run test Cardiopulmonary exercise test
Muscular strength	Handgrip strength Standing long jump tests
Speed and agility	4 × 10 shuttle run test
Flexibility	Sit-and-reach test
Attention capacity	d2 attention test Stroop task test
Physical activity enjoyment	Physical activity enjoyment scale
Potential confounders	
Physical activity and sedentary behavior	Actigraph GT1M, dual-axis accelerometer ActivPal
Dietary assessment	24-h diet record Food frequency questionnaires
Pubertal development (Tanner stage)	Questionnaire
Family medical history, demographic characteristics, socioeconomic status	Questionnaire

#### Primary outcome

The controlled attenuation parameter is the ultrasonic attenuation coefficient of the ultrasonic signals used during transient elastography examination and is expressed in decibels per meter (dB/m; range from 112 to 242 dB/m), acquired at a 3.5-MHz standard M probe (diameter 7 mm) with a FibroScan® 502 Touch Mode M. Before and during the examination, the adolescent will lie on their back with the right arm in maximum abduction, and abdominal ultrasound will be used to identify a region of the liver free of large vascular structures. The tip of the FibroScan® transducer will then be placed on the skin between the ribs over the right lobe of the liver, and the liver stiffness will be recorded. The technical background and reference values in the pediatric population (1 to 18 years) have been recently described in detail [36]. The algorithm is included in the transient elastography software and data are automatically calculated simultaneously with the liver stiffness measurement.

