**Methods/design:**

Altogether, 100 hundred overweight/obese, sedentary adolescents (aged 11–17 years) attending two public schools in Bogotá, Colombia, will be included in a parallel-group randomized controlled trial. Adolescents will be randomly assigned to an intervention group following one of four curricula: (1) the standard physical education curriculum (60 min per week of physical activity, *n* = 25) at low-to-moderate intensity; (2) a high-intensity physical education curriculum (HIPE, *n* = 25), consisting of endurance and resistance games and non-competitive activities, such as running, gymkhanas, lifting, pushing, wrestling, or hauling, for 60-min sessions, three times per week, with an energy expenditure goal of 300 to 500 kcal/session at 75–85% maximum heart rate (HRmax); (3) a low-to-moderate intensity physical education curriculum (LIPE, *n* = 25) consisting of endurance and resistance games and non-competitive activities (e.g., chasing, sprinting, dribbling, or hopping) for 60-min sessions, three times per week with an energy expenditure goal of 300 kcal/session at 55–75% HRmax; and (4) a combined HIPE and LIPE curriculum (*n* = 25). The HIPE, LIPE, and combined interventions were performed in addition to the standard physical education curriculum. The primary outcome for effectiveness is liver fat content, as measured by the controlled attenuation parameter 1 week after the end of the intervention program.

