### Power calculation and sample size

Change in liver fat is the primary outcome of this study. For liver fat measured by a FibroScan 502®, a sample size of 100 will have 80% power to detect a difference in hepatic fat of 5.0% assuming a standard deviation of 4.1% and an α of 0.025 for a two-sided significance level. Assuming a maximum a loss of follow-up of 10%, we decided to recruit a total of 100 subjects, 25 participants for each group. We assume that the dropout rate will be similar to that in our previous studies performed in a young overweight population with a similar age range and a similar intervention program [18, 23–25, 57–59]. The sample size will allow for multivariate analyses with up to three predictors, assuming moderate size effects.

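### The primary outcome is read in dB/m, but Table 2 and the power calculation state it in percent hepatic fat with no link between the two scales

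*Protocol article*

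**What the plan says.** Four places in the protocol article describe one endpoint on one device.

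- **Abstract, Methods/design:** "The primary outcome for effectiveness is liver fat content, as measured by the controlled attenuation parameter 1 week after the end" of the programme.
- **Data collection and outcome measures:** "The primary outcome measure is hepatic fat content, which will be assessed with the controlled attenuation parameter". Table 2 in that section gives the primary outcome the unit percent and names vibration-controlled transient elastography as the method.
- **Primary outcome:** CAP is an ultrasonic attenuation coefficient, acquired on a FibroScan 502, and "is expressed in decibels per meter (dB/m; range from 112 to 242 dB/m").
- **Power calculation and sample size:** "Change in liver fat is the primary outcome of this study". The calculation names the same FibroScan model and claims that "a sample size of 100 will have 80% power to detect a difference in hepatic fat of 5.0" percent. The SD entered is 4.1%, the two-sided α is 0.025, loss is put at no more than 10%, and each group has 25 participants.

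The Statistical analysis section calls the outcome hepatic fat and gives no unit.

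**The concern.** A coefficient in dB/m and a percentage of liver fat are different quantities. A difference and an SD given in one cannot be used in the other without a conversion, and the article contains none. The only algorithm mentioned is the device software that calculates the data automatically; it is not described as returning percent fat. Nor does the article say that 5.0% and 4.1% are proportional changes in the CAP reading.

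Two things are at stake. First, the sample-size justification cannot be verified for the variable that will be analysed. Second, results reported under the Table 2 label would be read as percent liver fat, a quantity that the description of the measurement does not support.

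**Working it through.** **1. Units side by side**

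| Place in the article | Variable | Unit |
|---|---|---|
| Primary outcome | CAP, FibroScan 502 | dB/m, 112 to 242 |
| Table 2 | Hepatic fat, transient elastography | percent |
| Power calculation and sample size | Liver fat, FibroScan 502 | percent (difference 5.0, SD 4.1) |
| Statistical analysis | Hepatic fat | none given |

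**2. The plan's own figure**

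Inputs from the sample-size section: difference 5.0, SD 4.1, two-sided α 0.025, power 80%, 25 per arm, 10% loss.

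- Standardised difference: 5.0 / 4.1 = 1.22.
- Normal approximation: n per arm = 2 × (2.241 + 0.842)² × (4.1 / 5.0)² = 12.8, so 13.
- t distribution: 14 per arm gives 79.6% and 15 gives 82.8%, so 15 per arm. That is 60 in four arms, or 68 after 10% loss (15 / 0.9 = 16.7, so 17 per arm).
- Power of a pairwise t test with 25 per arm: 97.5%.

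A pairwise comparison with these inputs does not reproduce 80% power at 100 participants; 100 is more than they require. That is a separate matter, and the surplus gives no assurance in dB/m.

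**3. What carries over to any scale**

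For two arms of n each, the detectable standardised difference e solves

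power = P(|T| > t with 2n − 2 degrees of freedom at 1 − 0.0125) = 0.80, where T is noncentral t with noncentrality e × √(n/2).

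- n = 25: e = 0.896.
- n = 22 (25 × 0.9 = 22.5, rounded down): e = 0.958.
- The normal approximation, (2.241 + 0.842) × √(2/n), gives 0.872 and 0.930.

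The detectable difference in dB/m is therefore 0.896 to 0.958 times the SD of CAP. The article gives no such SD, so no dB/m figure follows from it.

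**4. The reading as relative change**

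If 5.0% and 4.1% were fractions of a CAP value within the stated range:

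- difference: 0.05 × 112 = 5.6 to 0.05 × 242 = 12.1 dB/m;
- SD: 0.041 × 112 = 4.6 to 0.041 × 242 = 9.9 dB/m.

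The ratio stays at 1.22, so the power in step 2 would be unchanged, but only if an SD of 4.6 to 9.9 dB/m is realistic. The article offers nothing to judge that by.

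**The case against.** The best defence is that the sample-size section opens with change in liver fat and ties its figures to the FibroScan, so a percent change in the device reading may have been meant. The text does not exclude this. It is therefore too strong to say that the 5.0% and 4.1% certainly belong to some other quantity; the scale is unstated. Against the defence, Table 2 puts percent on the measure itself at baseline and post-test, and the sample-size section speaks of a difference in hepatic fat without mentioning relative change. If that reading was intended, it still has to be written down.

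A full protocol may contain a conversion that the article omits. But the article does state a unit, a difference and an SD, and as printed they conflict. That is more than an omission.

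Two stronger readings are tempting and not supported.

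- **The trial is underpowered on CAP.** This would need an SD in dB/m, which the article does not give. Guessing it from the 112 to 242 range does not help: the article does not say what that range represents, and a detectable difference quoted as a share of the range would merely follow from the guess. Baseline adjustment would also lower the detectable difference below the unadjusted figures.
- **The endpoint is a post-test level in one place and a change in another.** The abstract gives the timing of the measurement. The data collection and analysis sections set baseline and 6-month measurements compared in a repeated-measures model, which is compatible with change as the outcome.

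**Conclusion.** The unit conflict stands on the current text and concerns the primary endpoint. The planned difference, SD and 80% power are in percent, the device yields dB/m, and nothing printed joins them, so the power claim cannot be verified for the analysed variable.

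The size can be stated only in SD units: about 0.90 SD (25 per arm) to 0.96 SD (22 per arm). This assumes an unadjusted two-arm t test, two-sided α of 0.025, 80% power, equal arms and 10% loss. Whether that is an adequate difference in dB/m remains open. Because this is the basis of the primary analysis and is cheap to correct, it should be corrected.

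**What to change.** 1. Name CAP in dB/m as the analysed primary variable in Table 2, the Primary outcome section and the sample-size section.
2. Restate the sample-size section for the fixed 100 participants (25 per arm, about 22 after loss) as a detectable difference in dB/m: 0.90 to 0.96 times a CAP SD. Take that SD from the pooled, arm-blind baseline data or another stated source, and say whether it is the SD of a level or of a change.
3. If 5.0% and 4.1% were meant as relative change in CAP, say so and give the dB/m equivalents.
4. Word conclusions as change in CAP, not as percent liver fat.

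The repeated-measures model in the Statistical analysis section can stay; the unit conflict does not call for a different one.

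The cost is wording and one recalculation, with no added participants or measurements. The restated detectable difference may look less favourable than the present text.

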#### Secondary outcome measures

Blood samples will be obtained from each subject early in the morning by venipuncture from the antecubital vein, following a 10-h overnight fast. Blood samples will be drawn into a tube containing ~1.8 mg EDTA-K3 per mL blood for plasma and a tube with a polymer gel for serum determinations (Vacutainer, Becton Dickinson & Company 2017). Samples will be handled according to Clinical Laboratory Improvement Amendments, which must be followed to achieve valid test results that can be used for diagnoses [37]. Blood samples will be stored at room temperature until centrifugation. Samples should undergo centrifugation immediately. This will be carried out at 1500*g* for 15 min at 4 °C and will give three layers (from top to bottom): plasma, leukocytes (buffy coat), and erythrocytes. The supernatant (plasma) and serum will be carefully aspirated at room temperature and aliquoted into cryovials. Finally, both samples will be stored at −80 °C before the analysis of serum lipids, adipokines, aminotransferases, inflammatory biomarkers, uric acid, ferritin, albumin insulin, and neuronal function biomarkers using surface plasmon resonance biosensors.

Serum lipids, including high-density lipoprotein cholesterol (HDL-C), LDL-C, total cholesterol, and total triglyceride, will be measured with an automatic biochemical analyzer (Deyi Biomedical Technology Co., Ltd., Beijing, China). Concentrations of serum insulin and HbA1c will be analyzed with commercially available electrochemiluminescence immunoassay kits (Roche Diagnostics GmbH, Mannheim, Germany). The homeostatic model assessment of insulin resistance (HOMA-IR) and homeostatic model assessment of pancreatic β-cell function (HOMA-β) indices will be calculated with the following equation:$$ \mathrm{HOMA}-\mathrm{IR}=\mathrm{fasting}\ \mathrm{insulin}\ \left(\mathrm{FINS};\mathrm{Ins}0\right)\times \mathrm{fasting}\ \mathrm{blood}\ \mathrm{glucose}/22.5 $$

and$$ \mathrm{HOMA}-\beta =20\times \mathrm{Ins}0/\left(\mathrm{fasting}\ \mathrm{blood}\ \mathrm{glucose}-3.5\right) $$

Alanine aminotransferase, aspartate aminotransferase, and g-glutamyl transferase levels will be determined by enzymatic assays (Beckman Coulter, Brea, CA, United States). Uric acid, albumin, and ferritin will be measured in an enzymatic spectrophotometer (Beckman Coulter, Brea, CA, United States). All assays will be measured in duplicate according to the manufacturers’ standard procedures.

Non-traditional biomarkers will be evaluated for the presence and relative amounts of 80 different inflammatory markers using a Proteome Profiler Human Cytokine Array Panel A kit (R&D Systems, Minneapolis, MN) (Additional file 1: Table S1). These include: hs-C reactive protein, ENA-78, GCSF, GM-CSF, GRO, GRO-α, I-309, IL-1α, IL-1β, IL-2, IL-3, IL-4, IL-5, IL-6, IL-7, IL-8, IL-10, IL-12 p40/p70, IL-13, IL-15, IFN-γ, MCP-1, MCP-2, MCP-3, MCSF, MDC, MIG, MIP-1β, MIP-1δ, RANTES, SCF, SDF-1, TARC, TGF-β1, TNF-α, TNF-β, EGF, IGF-I, angiogenin, oncostatin M, thrombopoietin, VEGF-A, PDGF-BB, leptin, BDNF, BLC, Ckß8–1, eotaxin, eotaxin-2, eotaxin-3, FGF-4, FGF-6, FGF-7, FGF-9, Flt-3 ligand, fractalkine, GCP-2, GDNF, HGF, IGFBP-1, IGFBP-2, IGFBP-3, IGFBP-4, IL-16, IP-10, LIF, LIGHT, MCP-4, MIF, MIP-3α, NAP-2, NT-3, NT-4, osteopontin, osteoprotegerin, PARC, PLGF, TGF-β2, TGF-β3, TIMP-1, and TIMP-2.

This assay will be performed according to the instructions provided by the manufacturer. Briefly, 50–200 μL of serum samples will be thoroughly suspended in 1.5 mL of array buffer 5, incubated at room temperature for 15 min, and centrifuged for 5 min at 5000*g*. The supernatant (1 mL each) will be added to a cocktail of biotinylated antibodies and incubated at room temperature for 1 h. The sample/antibody mixture will be subsequently incubated at 4 °C for 19 h with a membrane embedded with antibodies specific to each of the 80 different inflammatory markers analyzed. The pixel densities of each blot (band), representing the amount of each inflammatory marker present, will be determined using the ImageJ software (National Institutes of Health, Bethesda, MD). These non-traditional biomarkers will be measured in a random sub-sample (*n* = 10, for each group).

Surface plasmon resonance allows real-time monitoring of NT-3, NT-4, and BDNF (R&D Systems, Minnesota, USA). In a typical experiment, the signal reflection, measured at a fixed angular position, is evaluated as a function of time. The real-time quantification will use a specific anti-protein antibody/protein. All experiments will be carried out at 25 °C using a Biacore 2000 instrument with a CM5 chip (Biacore, Uppsala, Sweden). HBS-EB buffer (10 mM 4-(2 hydroxyethyl) piperazine-1-ethanesulfonic acid [HEPES], 150 mM NaCl, 3 mM ethylene diamine tetraacetic acid [EDTA], 0.005% Tween 20, pH 7.4) will be used as a continuous running buffer at a 5–60 μg/mL flow rate. The antibodies (ligand) anti-NT-3, anti-NT-4, and anti-BDNF will be immobilized onto the CM5 sensor surface at a concentration range of 10–50 μg/mL. Before immobilization of the antibodies, the sensor surface will be activated via an amino-coupling chemistry kit [1-ethyl-3-(3′-dimethylaminopropyl) carbodiimide, N-hydroxysuccinimide (GE Healthcare, Uppsala, Sweden)]. For the immobilization steps, the basic principles of assays using surface plasmon resonance will be applied, such as preconcentration and a binding assay with the analyte. Each antibody solution will be injected individually to couple with the activated surface until the appropriate immobilization level is achieved. Activated carboxyl group excess will be blocked by 1 M ethanolamine hydrochloride (pH 8.5). A reference or control flow cell with 50 μg/mL bovine serum albumin (Sigma-Aldrich, Saint Louis, MO) at pH 5.0, but no immobilizing solution, will be used to subtract the instrument systematic noise and drift (background response). After each injection of a binding assay with the analyte and standard samples, an optimal regeneration solution will be injected in agreement with previous studies [38, 39]. The percentage of surface regeneration will be estimated using [1 − (Rreg/Ro) × 100]. If the percentage regeneration achieved is below 10%, other regeneration solutions should be injected until the percentage regeneration is higher than 50%. Standard curves will be constructed by dilution of each standard recombinant protein NT-3, NT-4, and BDNF. A range of 20–5000 ng/mL will be used to obtain the curve. Each sample of protein will be injected in triplicate.

Diluted plasma samples will be quantified and the binding response will be calculated by subtracting the response measured in the control flow cell from the response in the sample flow cell. This value is applied to the simple 1 : 1 L binding model (A + B or AB). The Langmuir model is the most commonly used model for calculating binding affinity. The report points will be taken 10 s before and 100 s after taking a measurement and the difference between these two report points will be taken as the end-point measurement.

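### The biosensor regeneration formula is misbracketed, and its 10% trigger and 50% target leave a first result of 10–50% without any action

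*Protocol article*

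**What the plan says.** The surface plasmon resonance text under Secondary outcome measures describes a sensor chip that is reused. "After each injection of a binding assay with the analyte and standard samples, an optimal regeneration solution will be injected", with a reference to earlier studies. Success is then measured: "The percentage of surface regeneration will be estimated using [1 − (Rreg/Ro) × 100", where the printed bracket closes directly after the 100. Neither Rreg nor Ro is defined.

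The next sentence is the decision rule: "If the percentage regeneration achieved is below 10%, other regeneration solutions should be injected until the percentage regeneration is higher than 50" per cent. The article states no action for a first result between those two figures.

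For the read-out, one report point is taken before and one after, and "the difference between these two report points will be taken as the end-point measurement". The response of a control flow cell is also subtracted. That cell carries bovine serum albumin and no immobilising solution.

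The analytes are a named objective. Data collection and outcome measures lists NT-3, NT-4 and "brain-derived neurotrophic factor (BDNF) levels (second secondary objective").

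**The concern.** There are two faults in consecutive sentences, and mending the first does not mend the second.

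First, the multiplication by 100 applies to the ratio only, so the result is not a percentage. It cannot sensibly be compared with 10% or 50%, and the undefined symbols give the reader nothing to resolve it with.

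Second, the rule uses one figure to start action and a different, much higher figure to end it. The plan thereby treats 50% or less as inadequate for a chip that first scored 9%, and asks for nothing when a chip first scores 12%.

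What is at stake is antibody capacity. If analyte stays bound, fewer sites are free for the next injection, and the same concentration can give a smaller response. The before/after difference removes a residual offset but does not bring back occupied sites. The control cell, as described, has no capture antibody and so cannot track their loss. Regeneration follows injections of standards as well as samples, so the calibration curve passes through the same check.

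**Working it through.** **Inputs from the document.** The printed expression; a trigger below 10%; a target above 50%.

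**Assumption.** Rreg is the response left after regeneration and Ro the response before it, so r = Rreg/Ro lies between 0 and 1. The article reports no regeneration result, so there is no stated figure to reproduce.

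**Step 1: the two formulas.** Printed: 1 − 100r. Bracket moved: (1 − r) × 100.

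| r (share still bound) | Printed | Bracket moved | Rule applied to the moved bracket |
|---|---|---|---|
| 0 | 1 | 100% | above target |
| 0.05 | −4 | 95% | above target |
| 0.10 | −9 | 90% | above target |
| 0.50 | −49 | 50% | no action stated |
| 0.70 | −69 | 30% | no action stated |
| 0.91 | −90 | 9% | act until above 50% |
| 1 | −99 | 0% | act until above 50% |

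**Step 2: can the printed formula meet the rule?** In percent, 1 − 100r > 50 needs r < (1 − 50)/100 = −0.49, and even reaching 10 needs r = (1 − 10)/100 = −0.09. Neither is possible for r ≥ 0: every result is below 10 and none exceeds 50. If the output is instead read as a proportion, 1 − 100r > 0.5 needs r < 0.005, which is more than 99.5% removal. The target therefore means something unreachable, more than 99.5% removal, or (bracket moved) more than 50% removal, depending on the reading.

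**Step 3: the gap with the bracket moved.** Trigger: (1 − r) × 100 < 10, so r > 0.90. Target: (1 − r) × 100 > 50, so r < 0.50. For r from 0.50 to 0.90 the rule requires nothing, and 50% to 90% of the bound signal remains.

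**Step 4: what the gap could allow (illustration only).** Assume that each injection fills a fraction f of the free sites, that every cycle regenerates by the same g, and that nothing dissociates otherwise. With b the occupied share before an injection, the response is f(1 − b), and b then becomes (b + response)(1 − g). For f = 0.3 and g = 0.10:

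- first response 0.300, after which b = 0.300 × 0.9 = 0.270
- second response 0.3 × 0.730 = 0.219, after which b = 0.489 × 0.9 = 0.440
- third response 0.3 × 0.560 = 0.168
- third relative to first: 0.168/0.300 = 0.56

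| Regeneration g | f = 0.1 | f = 0.3 | f = 0.5 |
|---|---|---|---|
| 10% | 0.84 | 0.56 | 0.35 |
| 50% | 0.93 | 0.80 | 0.69 |
| 90% | 0.99 | 0.97 | 0.95 |

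Entries are the third of three identical injections relative to the first. The values of f and the constant g are not in the article.

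**The case against.** The strongest reply is that this is a typesetting slip in a condensed article. A laboratory asked for a percentage would not act on −49 and would use (1 − Rreg/Ro) × 100. A chip with 95% removed then scores 95% and passes. The text asks for an optimal regeneration solution each time, and an operations manual that is not shown may hold the bench criteria. Perhaps 10% is only the point at which to change the solution, with above 50% the level sought throughout. Triplicate injections would also expose a large decline.

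Most of this stands as a limit on the consequence. A reader might infer that the assay must either fail its own check every time or run on a chip still loaded with the previous sample. The document does not support that: under the evident formula a well-regenerated chip passes, and the rule leaves poor regeneration unaddressed without producing it. A reader might also infer a bias between arms or between visits. That would need run order to be linked to arm or visit. The article does not say it is, and outcome personnel are described as blinded to allocation. The decline figures rest on assumed f, and the worst of them need 10% regeneration in every cycle.

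The reply does not remove the defect. The formula and both thresholds are printed, so this is a misstatement and not detail left to a manual. Reading 50% as the level always sought is reasonable, but the sentence attaches it only to chips that first fell below 10%.

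**Conclusion.** The point holds as an error in a stated quality rule. The printed formula cannot exceed 1 for a non-negative ratio, so in percent its target is unreachable, and its terms are undefined. With the evident formula, a first result of 10% to 50% proceeds without action although 50% to 90% of the bound signal remains, while a slightly lower first result must be raised above 50%.

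The rule permits loss of binding capacity and does not by itself cause it. If loss occurred, the before/after difference and the antibody-free control cell would not correct it. Its actual size cannot be derived from the article. The conclusion assumes that Rreg and Ro mean the response after and before regeneration. It concerns only NT-3, NT-4 and BDNF; hepatic fat and the sample size are unaffected.

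**What to change.** Write the formula as (1 − Rreg/Ro) × 100. Define Rreg as the response left after regeneration and Ro as the response before it. Replace the two figures by one threshold that serves both as trigger and as acceptance level, and repeat regeneration until it is met. The threshold should be no lower than the plan's own 50% target. The article gives no basis for a particular higher figure, so the laboratory should justify the level it chooses.

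The cost is one corrected line, two definitions and one reconciled threshold in the laboratory procedure, plus a few extra regeneration injections.
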